### Randomisation, blinding and allocation concealment

Eligible participants will be randomised to Mobility and Strength Training or Mobility and Strength Training with protein supplements using a secure (encrypted) centralised web-based randomisation service provided by the Oxford Clinical Trials Unit (OCTRU). Randomisation will be 1:1, stratified by frailty (pre-frail/frail) using variable block sizes within each strata. Following randomisation, the physiotherapy team and the central study team will be notified of allocation
*via* automated email. As we are not using a placebo supplement, it is not possible to blind the participants or physiotherapists delivering the interventions (including provision of supplements). Outcome assessors will be blinded to treatment allocation.

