### Interventions

The schedule of intervention delivery is outlined in
Table 3.

**Table 3. T3:** Intervention delivery schedule.

	Mobility and Strength Training	Training + Protein Supplements
Individual pre-class appointment		
Assessment by physiotherapist to establish current ability and exercise setting. Home exercise diary introduced.	X	x
Assessment by physiotherapist to discuss protein supplement dosing and instructions. Provided with written instructions and introduced to protein supplement diary.		x
Delivery of protein supplement arranged.		x
Weeks 1–16		
Weekly group mobility and strength exercises • Group discussion including behavioural strategies to encourage adherence with home exercises (goal setting, exercise planning and problem solving) (15 minutes) • Seated warm up (5 minutes) • Exercise circuit (20 minutes): Strengthening exercises: knee extension, hip extension and abduction, sit to stand Combined hip flexor and calf stretch Balance exercise • Walking circuit (20 minutes) One session of home exercises each week (exercise diary completed). Weights for home exercises are provided if appropriate.	x	x
Protein supplements taken daily. Complete supplement diary.		x
Protein Supplement Reviews including weight checks undertaken at weeks 2, 4, 8, 12 and 16 of the programme. Referral to dietitian if needed.		x
Weeks 17–24		
Twice weekly home exercises. Complete exercise diary.	x	x
3 follow up telephone calls to review progress with home exercises conducted by physiotherapist.	X	x
Protein supplements taken daily. Complete supplement diary.		x
3 telephone supplement reviews during the follow up telephone calls. Weight is not to be monitored.		x

**
*Mobility and Strength Training.*
** All participants will be asked to undertake twice weekly mobility and strength training supported by a physiotherapist for 24 weeks using a combination of weekly group exercise (16 weeks) and home exercises (8 weeks). Group sessions are used to provide supervision and support to participants and promote adherence to long term exercise. This is a pragmatic approach to strength and mobility training that can be implemented within NHS physiotherapy departments without the need for specialist exercise equipment. We have delivered a similar programme for participants with mobility limitations due to spinal stenosis, which was well attended, the exercises were well tolerated and enjoyed by participants
^
13,
34
^.

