^. If a participant has a BMI of 30 or more, then the recommended dose of protein is 75% of the calculated amount based on weight (as per usual clinical practice)
^
38
^. Additionally, if a participant has an eGFR between 30-60 ml/min/1.73 m
^2 ^(indicating a moderate reduction in renal function), protein intake will be limited to 1.3 g/kgBW/day. This is the maximum dose recommended for this patient group by The Kidney Disease Improving Global Outcomes (KDIGO) guidelines.

On a day when participants undertake Mobility and Strength training (at the hospital or at home), they will be advised to take one of their drinks of the supplement directly after the exercise session. Participants will complete a protein supplement diary to monitor adherence and record any side-effects experienced. Participants will be monitored and weighed at regular reviews (
Table 3). If a participant is experiencing gastro-intestinal problems, then they will be advised to reduce the dose by a half and gradually increase the dose back to the recommended amount over four days to improve tolerance. If a participant has lost >10% of their weight or is reporting ongoing intolerance issues, then participants will be reviewed by the main study team dietitian to decide if the protein supplement dose needs to be adjusted or other dietary advice given.

The chosen supplement also contains vitamin D and calcium. If participants are already taking over the counter supplements, then they will be asked to stop taking them while they are on the protein supplements. If participants are already on prescribed supplements, then the physiotherapist will liaise with the participant’s general practitioner to adjust their prescription to ensure daily maximum doses are not exceeded (Vitamin D: maximum of 4,000 IU per day; Calcium: maximum of 1 g per day).

All participants will attend the same exercise sessions. Supplement reviews will be conducted outside these sessions and participants will be asked not to discuss them in the groups. Groups will be run this way to so sites can fill the exercise groups in a timely way.

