### Adverse events

Safety reporting will begin from the time of randomisation to 8 month follow up. All study staff have been trained to report adverse events (AEs) related to the study interventions. Given the age of participants, there are foreseeable AEs that should only be reported if they occur during or within two hours of any study interventions. These include acute infections, medical instability (
*e.g.*, worsening of heart failure), vestibular disorders or stroke and fall-related injuries. We anticipate participants may experience delayed onset muscle soreness (<72 hours) upon starting a new exercise programme, which is only reported if they are more persistent or severe than expected. We would also expect that participants taking protein supplements may experience mild gastrointestinal complaints including diarrhoea, constipation, bloating and loss of appetite. Participants are made aware of these, and they should be short lived and managed by adjusting their protein supplement dose. If symptoms are more severe and longer lasting than what is expected, then they will be reportable.

A serious adverse event (SAE) is an untoward medical occurrence that results in death; is life-threatening; requires inpatient hospitalisation or prolongation of existing hospitalisation; results in persistent or significant disability/incapacity; consists of a congenital anomaly or birth defect. We will follow reporting procedures in accordance with Good Clinical Practice (GCP) to report any SAEs that are potentially related to trial procedures.

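### The related-only and two-hour reporting rules make reported adverse events a poor by-arm safety input to the progression decision; an unfiltered descriptive table would mend this cheaply

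*Protocol article*

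**What the plan says.** The Adverse events section of the protocol article sets three limits on what is reported between randomisation and 8 months.

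- Adverse events: "All study staff have been trained to report adverse events (AEs) related to the study interventions".
- Foreseeable events (acute infections, medical instability such as worsening heart failure, vestibular disorders or stroke, fall-related injuries): "foreseeable AEs that should only be reported if they occur during or within two hours of any study interventions".
- Serious adverse events: good clinical practice procedures are followed "to report any SAEs that are potentially related to trial procedures".

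Muscle soreness and mild gastrointestinal complaints have separate rules. They become reportable only when worse or longer lasting than expected.

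Under Primary feasibility outcomes, progression rests on the stop-go criteria together with adverse events and discussion with the Independent Monitoring Committee. Statistical methods lists safety monitoring among the descriptive outcomes.

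Exposure differs by design. On exercise, "All participants will be asked to undertake twice weekly mobility and strength training supported by a physiotherapist for 24 weeks". Only one arm also takes supplements every day for 24 weeks. On training days in that arm, "they will be advised to take one of their drinks of the supplement directly after the exercise session", which implies that some participants have more than one drink a day. Table 3 gives that arm alone "Protein Supplement Reviews including weight checks undertaken at weeks 2, 4, 8, 12 and 16 of the programme".

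On blinding, "the physiotherapy team and the central study team will be notified of allocation".

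**The concern.** The foreseeable list holds some of the events that matter most in frail older adults, and the rule for reporting them depends on the clock. A person is under observation for eight months but inside the window for only a small part of it. For exercise the rule has some logic, since a fall or collapse caused by a session is likely to come during it or soon after. It has much less logic for a supplement taken daily for 24 weeks, and the supplement is the only component that differs between the arms. Medical instability caused by the supplement, for example, need not appear within two hours of a drink.

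Because the window is tied to exposure, its length may also differ between arms. The committee could then be weighing a small, selected set of events whose selection is not the same in both arms, with no stated unfiltered count beside it. At stake is how informative the safety part of the progression decision is, and whether the definitive trial inherits usable background rates.

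**Working it through.** The plan gives no figure on this point, so there is none to reproduce. The check counts reportable hours per participant under the two-hour rule.

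**Inputs from the article**
- Sessions (Table 3): 16 group + 16 home in weeks 1–16, then 2 × 8 = 16 home in weeks 17–24. Total 48, the same in both arms.
- Group session length (Table 3): 15 + 5 + 20 + 20 = 60 minutes.
- Supplement days: 24 × 7 = 168, one arm only.
- Protein per serving: 20.7 g. Target: up to 1.6 g/kg/day, or 1.3 g/kg/day with eGFR 30–60.
- Sample size: 50, about 25 per arm.

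**Assumptions**
- The window is the session plus the two hours after it.
- Home sessions also last 1 hour, and adherence is full.
- Eight months = 8 × 30.4375 = 243.5 days = 5,844 hours, with training starting at randomisation.
- On the 48 training days one drink directly follows exercise, so its window is already counted.
- Events occur at random times, at the same rate in both arms.

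**Reportable hours**
- Training arm: 48 × (1 + 2) = 144 h; 144/5,844 = 2.5%.
- Supplement arm, drinks not counted as interventions: 144 h; ratio 1.
- One drink a day, each counted: 144 + (168 − 48) × 2 = 384 h; 6.6%; ratio 384/144 = 2.7.
- Two separate drinks a day: 384 + 168 × 2 = 720 h; 12.3%; ratio 720/144 = 5.0.

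Events outside the window are therefore 97.5% in the training arm, and 93.4% or 87.7% in the supplement arm with one or two drinks.

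**Sensitivity**
- 45-minute home sessions: training time is 16 × 3 + 32 × 2.75 = 136 h, and the ratios become 376/136 = 2.8 and 712/136 = 5.2.
- 70% supplement adherence: (144 + 0.7 × 240)/144 = 2.2 and (144 + 0.7 × 576)/144 = 3.8.
- Three separate drinks: 720 + 336 = 1,056 h; 18.1%; ratio 7.3; 82% outside.

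**Is more than one drink plausible?** For an assumed 70 kg participant eating 0.9 g/kg/day, the gap is (1.6 − 0.9) × 70/20.7 = 2.4 servings, or (1.3 − 0.9) × 70/20.7 = 1.4 under the renal limit. So yes, although the article gives no number and servings could be taken together.

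**After week 24.** 243.5 − 168 = 75.5 days, 31% of follow-up, have no scheduled intervention. No foreseeable event meets the rule then.

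**Absolute size.** With an assumed 5 foreseeable events per arm, the rule catches 5 × 0.0246 = 0.12 in the training arm. In the supplement arm it catches 0.12 if drinks do not count, and 5 × 0.0657 = 0.33 or 5 × 0.1232 = 0.62 if they do. The gap between arms is at most about half an event; nearly all the loss is common to both.

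**Precision of an unfiltered table.** The 95% half-width for a difference between arms is 1.96 × √(2p(1 − p)/25). At assumed admission rates of 10%, 20% and 30% it is 17, 22 and 25 percentage points.

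**The case against.** The strongest objection is that this asks for a table, and safety tables are normally left to an analysis plan or full protocol that is not shown. That holds for layout. It does not reach the reporting rules, which the article itself fixes and which decide which events can enter any table of reported events.

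A reader might infer that the rules will produce an excess of reported events in the supplement arm. The documents do not support that.

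- The unequal window requires every drink to count as a study intervention. The nearest wording, "physiotherapists delivering the interventions (including provision of supplements", concerns what physiotherapists provide and does not settle whether a drink taken at home counts. If it does not, the windows are equal.
- The rule for mild gastrointestinal complaints removes events expected in the supplement arm, which pulls the other way.
- The extra contact is modest. Both arms have one pre-class appointment, 16 group sessions and 3 calls, 20 contacts in all. The supplement arm has 25, because its later reviews take place within the same calls.
- Staff know allocation, but the article does not say who judges relatedness, so biased attribution is conjecture.

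A reader might also infer that unrelated serious events go unrecorded. The sentence on serious events may describe onward reporting only, and a serious foreseeable event outside the window may still be reported if judged related.

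It is also fair that no stop-go threshold uses event counts, and that falls, eGFR and service use are collected in both arms without these filters. The article does not, however, connect those data to the safety part of progression.

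**Conclusion.** The point holds as a minor one. The stated rules leave out about 88% or more of randomly timed foreseeable events in either arm, given up to two separate drinks a day (82% with three). They also suit a 24-week daily supplement poorly. Reported adverse events are therefore a thin and selective basis for comparing safety by arm before progression.

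Random timing is the main assumption behind these percentages. Falls and collapses provoked by exercise would cluster inside the window and be caught more often.

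Reportable time may be 2.7 to 5.0 times as long in the supplement arm at full adherence if each drink counts, or the same if not. The net direction of any imbalance in reported events is unknown, and the expected gap is a fraction of an event. Nothing here shows that the progression decision would change. The case for acting is that unfiltered data are largely being collected already.

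**What to change.** Leave expedited reporting as it is. Add wording such as:

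*Before the progression decision, the Independent Monitoring Committee will receive a descriptive table by randomised arm, covering randomisation to 8 months and regardless of relatedness or timing, of known deaths, inpatient admissions, ProFANE falls and injuries, and 8-month eGFR. Related serious adverse events will be shown as a subset, with the number of participants missing for each item.*

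Admissions can come from the Client Service Receipt Inventory, if the version used covers them over the whole period, supplemented by withdrawal reasons. The falls item is needed because deaths and admissions alone would not recover fall injuries that did not lead to admission. Infections and vestibular events without admission would still be missed. It would also help to state whether taking a drink counts as a study intervention for the two-hour rule.

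The cost is a few sentences and one table, mainly from planned data. The table will include background events unrelated to the trial and will be imprecise at about 25 per arm. Falls and service use are self-reported by unblinded participants. Follow-up items will be missing for those lost: 0.15 × 50 = 7.5, so 7 or 8 people, at 15% loss, and 0.30 × 50 = 15 at 30%. It should be labelled descriptive, with no test between arms.

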### Sample size

Given this is a feasibility study to inform the design of a definitive study, the sample size was determined from a recent simulation study of sample size requirements in pilot RCTs
^
39
^. A total of 50 measured subjects are recommended to calculate key design parameters (namely, standard deviation around the primary outcome measure for a definitive trial) and subsequently establish the definitive study sample size. Therefore, the target sample size for this study is 50 patients.

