## Abstract

Background Frailty is a common syndrome affecting older people and puts them at risk of hospitalisation, needing care or death. First signs of frailty include reduced muscle strength and mobility decline. A key cause of mobility decline as we age is sarcopenia (age related reduction in muscle strength and mass). Poor nutrition contributes to sarcopenia. A shortfall in protein is associated with reduced muscle mass and strength. This may be due to inadequate intake but also because older people have higher protein needs, especially those with multimorbidity. We need to develop effective treatment to reduce or slow the onset of frailty and mobility decline. Exercise is a recommended treatment. Protein supplements to address the shortfall in protein have the potential to enhance the benefit of regular exercise in frail or pre-frail older adults. This has yet to be definitively demonstrated. Aim To establish the feasibility of conducting an RCT evaluating mobility and strength training with or without protein supplements for people over 60 years old who are frail or pre-frail with a low protein intake. Methods A multicentre, parallel, 2-group, feasibility RCT. Participants (recruitment target = 50) with problems walking, low protein intake and classified as frail or pre-frail will be recruited from four NHS Physiotherapy community services. Participants will be randomised (secure computer-generated: 1:1) to receive 24 weeks of mobility and strength training (delivered in 16 group sessions plus home exercises) or 24 weeks of mobility and strength training with daily protein supplements. Primary feasibility objectives are to estimate 1) ability to screen and recruit eligible participants, 2) intervention fidelity, adherence, and tolerance and 3) retention of participants at follow up. Secondary objectives are to 1) test data collection procedures, 2) assess data completeness and 3) confirm sample size calculation for a definitive RCT. Registration ISRCTN Registry (ISRCTN30405954; 18/10/2022).

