^ and assessment of protein intake will be completed as well as taking a blood test to check renal function if required. We will obtain permission from the participants to inform their GP of their participation. Researchers responsible for consenting participants will be trained in consent procedures and been delegated to do so by the site Principal Investigator.

Estimated daily protein intake will be established by taking the average of two 24-hour dietary assessments using an online dietary assessment tool (myfood24.org)
^
20
^. The first dietary analysis is completed during this appointment. If protein intake is >1.4 g protein/kgBW/day for the first assessment, then they will be excluded at this point as it is unlikely their second dietary assessment will result in an average intake of <1.0 g protein/kgBW/day. The second dietary assessment will be completed after the appointment, which potential participants can complete online or with help from the central study team dietitian over the telephone.

If the participant has not had a blood test in the last three months to check their renal function, then a capillary blood sample will be taken to test Estimated Glomerular Filtration Rate (eGFR) using test kits provided Medichecks.com Ltd. The participant will be asked to complete a baseline questionnaire and undergo physical tests (
Table 2).

**Table 2. T2:** Data collection.

Domain	Measure	Baseline	Weeks 1–16	Weeks 17–24	8 month follow up
Demographic	Date of birth, sex, ethnicity, relationship status, height and weight * (body mass index), index of deprivation (postcode), type of housing, work status, education, carer needs, household income.	x			Height, weight only
Physical capacity	Short Physical Performance Battery (SPPB) ^ 21 ^ (proposed primary outcome)				
Mobility	6-minute Walk Test * ^ 22 ^	x			x
Muscle strength and sarcopenia	Hand grip * ^ 23 ^ and quadriceps strength * ^ 24 ^ measured using dynamometer SARC-F Questionnaire ^ 25 ^	x			x
Frailty	Tilburg Frailty Indicator (TFI) ^ 26 ^ Clinical Frailty Scale Health Questionnaire to calculate the Clinical Frailty Scale Score) ^ 27 ^ Fried Frailty Index based on self-report ^ 28 ^	x			x
Falls	Prevention of Falls Network Europe (ProFANE) self-report of falls and injuries ^ 29 ^	x			x
Comorbidities	Nordic pain questionnaire ^ 25, 26, 30 ^; self-reported health conditions ^ 31 ^	x			x
Protein intake	Assessment of daily dietary protein intake (myfood24.org)	x			x

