### Primary feasibility outcomes

**
*Progression criteria.*
** Progression criteria into a future definitive trial will be based on the stop-go criteria assessing feasibility detailed in
Table 4 alongside consideration of adverse events and discussions with the Independent Monitoring Committee. The stop-go criteria follow a ‘traffic light’ system: Red (stop), Amber (proceed with modifications) and Green (Go). There are four categories: recruitment, intervention fidelity, intervention adherence and study retention.

**Table 4. T4:** Stop-Go Criteria.

	Red	Amber	Green
Recruitment: Number of participants recruited	< 25 participants recruited within 6 months	25–39 participants recruited within 6 months	>40 participants recruited within 6 months
Intervention fidelity: provision of the mobility and strength training	<50% undergo their individual assessment and are allocated to their group sessions	50% – 80% of participants undergo their individual assessment and are allocated to their group sessions	>80% of participants undergo their individual assessment and are allocated to their group sessions
Intervention fidelity: delivery of the mobility and strength training (fidelity assessment *via* observations based on core criteria checklist)	<50% of all key criteria are met during observed sessions	50–80% of key criteria are met during observed sessions	>80% of key criteria are met during observed sessions
Intervention fidelity: protein supplements	<50% of participants receive the protein supplements *via* home delivery as intended	50–80% of participants receive the protein supplements *via* home delivery as intended	>80% of participants receive the protein supplements *via* home delivery as intended
Intervention adherence: participant attendance at the mobility and strength training	On average, < 8/16 sessions (50%) of sessions attended by 70% or more participants	On average, 8-10/16 session (50–69%) of sessions attended by 70% or more participants	On average, at least 11/16 sessions (70%) attended by 70% or more of participants
Intervention adherence: participant adherence to the protein supplements	On average, 70% or more participants report taking protein supplements on <50% of days over 24 weeks	On average, 70% or more participants report taking protein supplements on 50–70% of days over 24 weeks	On average, 70% or more participants report taking protein supplements on ≥70% of days over 24 weeks

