Study retention: follow up rates and checking for differential loss to follow up	>30% loss to follow up at 8 months in either study arm.	29–15% loss to follow up at 8 months in either study arm.	<15% loss to follow up at 8 months in both study arms.

Recruitment: We will collect data on screening and recruitment of eligible patients from each site on a monthly basis alongside reasons for exclusion.

Intervention fidelity: Physiotherapists will record intervention provision on an intervention log, which will be monitored to assess treatment fidelity. We will also observe or record intervention sessions and assess the delivery of the interventions using a checklist of the core criteria of the intervention. We will monitor protein supplement delivery to ensure supplements are delivered to participants as intended. The central study team will also visit up to 20% of participants at home to observe home exercises and check on protein supplement intake.

Adherence with the intervention: Attendance at the exercise classes is monitored using intervention logs completed by the physiotherapists. Participants will be asked to record when they take the protein supplements in their supplement diary.

Study retention: Follow up rates will be collected, and we will evaluate if there is any differential loss to follow up by study group.

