### Withdrawals of participants

During the trial, all participants have the right to withdraw at any time. In addition, site staff or the central team dietitian may discontinue a participant from a specific part of the intervention if they consider it necessary. Participants may withdraw from either protein supplements or exercise (but continue with the other part of the programme where applicable). They may also withdraw from the study including any further follow up assessments. Withdrawn participants will not be replaced.

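### The recruitment target of 50 is taken directly from a need for 50 measured subjects, which holds at 8 months only if nobody is lost; the effect on SD precision is modest

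*Protocol article*

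**What the plan says.** All references are to the protocol article.

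- **Sample size.** Citing a simulation study of pilot trials, the section says "A total of 50 measured subjects are recommended to calculate key design parameters". It names the main parameter as the "standard deviation around the primary outcome measure for a definitive trial". It then concludes: "Therefore, the target sample size for this study is 50 patients".
- **Abstract.** The 50 is a recruitment figure: "Participants (recruitment target = 50) with problems walking".
- **Withdrawals of participants.** Participants may leave follow-up altogether, and "Withdrawn participants will not be replaced".
- **Primary feasibility outcomes, Table 4.** Retention is Green with "<15% loss to follow up at 8 months in both study arms", Amber with 15–29% in either arm, and Red above 30% in either arm. Amber means going ahead with modifications.
- **Secondary exploratory outcomes.** Clinical outcomes collected at baseline and 8 months are to inform the definitive sample size, based on the SPPB as proposed primary outcome.

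**The concern.** The premise counts people measured and the conclusion counts people recruited. The two are equal only if every randomised participant provides the outcome. The protocol does not plan on that basis: it provides for withdrawal from follow-up, rules out replacement, and counts some loss as fully acceptable retention. The study could therefore be Green on retention, recruit all 50, and still fall short of the number on which its size is justified.

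At stake is the SD that will size the definitive trial. Confirming that sample size calculation is a named secondary objective. Required sample size is proportional to the variance, so imprecision in the SD carries over squared.

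**Working it through.** **Inputs**

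- Measured subjects recommended: 50 (Sample size).
- Recruitment target: 50 (Sample size; Abstract).
- Allocation 1:1, so 25 per arm (Randomisation, blinding and allocation concealment).
- Replacement: none (Withdrawals of participants).
- Loss bands per arm: Green below 15%, Amber 15–29%, Red above 30% (Table 4).
- Assumption: the SD of interest is the pooled within-arm SD of 8-month SPPB, with n − 2 degrees of freedom and approximate normality.

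**Step 1. Reproduce the stated target.** Number to recruit = 50 / (1 − loss), rounded up.

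| Loss | 50 / (1 − loss) | Recruit |
|---|---|---|
| 0% | 50.0 | 50 |
| 5% | 52.6 | 53 |
| 10% | 55.6 | 56 |
| 15% | 58.8 | 59 |
| 29% | 70.4 | 71 |

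The stated 50 is returned only at zero loss.

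**Step 2. Number measured with 50 recruited and no replacement.**

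- Most loss still Green: 3/25 = 12%, whereas 4/25 = 16% is Amber. Measured: 22 + 22 = 44.
- With a slightly uneven split of 23 and 27, the Green limit is 3/23 = 13.0% and 4/27 = 14.8%. Measured: 20 + 23 = 43. Hence about 43–44.
- Most loss still Amber: 7/25 = 28%, whereas 8/25 = 32% is Red. Measured: 18 + 18 = 36.

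**Step 3. Precision of the pooled SD.** As multiples of the estimate, the 95% limits are √(df / χ²₀.₉₇₅) and √(df / χ²₀.₀₂₅), with df = n − 2. The approximate relative standard error is 1/√(2·df). The upper limit for the implied definitive sample size is the square of the upper SD factor.

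| Measured | df | χ²₀.₉₇₅ | χ²₀.₀₂₅ | SD limits | Relative SE | Upper factor on definitive N |
|---|---|---|---|---|---|---|
| 50 | 48 | 69.02 | 30.76 | 0.83 to 1.25 | 10.2% | 1.56 |
| 44 | 42 | 61.78 | 26.00 | 0.82 to 1.27 | 10.9% | 1.62 |
| 36 | 34 | 51.97 | 19.81 | 0.81 to 1.31 | 12.1% | 1.72 |

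**Step 4. The part due to attrition.** Most of the uncertainty is already there with 50 measured. Loss adds 1.62/1.56, about 3.5% before rounding, to the upper factor on N at the Green limit, and 1.72/1.56, about 10%, in the Amber case.

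**The case against.** The best defence is that the Sample size section names no time point. A baseline SPPB SD could use all 50 participants, and then no shortfall arises. That is true of a baseline SD, but it does not rescue the derivation. The Secondary exploratory outcomes section uses 8-month data as well to inform the definitive sample size, and any 8-month or change-score SD needs completers. Whether the cited simulation study's 50 already allows for loss cannot be checked from the protocol; the word used there, measured, suggests that it does not.

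A second defence is that the bands in Table 4 are decision thresholds, not forecasts, and that Amber is conditional. This stands. The protocol gives no expected attrition rate, so 44 and 36 are illustrations at the edges of its own bands. The shortfall does not depend on Amber, since it already appears within Green.

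A third defence is that the consequence is small and the primary objectives are descriptive. This also stands, and it limits the weight of the point.

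Four stronger readings are tempting but unsupported:

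- **That the study could finish Green with only 41 recruited, and so with far fewer measured.** The Green criterion of ">40 participants recruited within 6 months" is a six-month progression threshold. Nothing says recruitment stops there, and the target remains 50.
- **That the protocol understates its uncertainty.** It gives no interval or margin for the SD, so there is no stated precision to be wrong.
- **That the SPPB has no scheduled visit because its row in Table 2 carries no marks.** The table may have lost entries when the text was extracted, and the timing is given elsewhere.
- **That the definitive trial must be sized from an upper confidence limit.** That is a design preference for a later trial, not a correction of this one.

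**Conclusion.** The derivation is wrong as written. A requirement for 50 measured subjects does not lead to a target of 50 recruited when loss is anticipated and withdrawals are not replaced. At 8 months the stated basis is met only with zero loss. At the edges of the protocol's own bands, with 25 per arm, 44 (Green) or 36 (Amber) would be measured.

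The effect is modest: the upper 95% factor for the SD goes from 1.25 to 1.27 or 1.31. The primary feasibility aims, which concern recruitment, fidelity, adherence and retention, do not depend on having 50 measured. The point is minor to moderate.

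The conclusion rests on reading measured as having 8-month SPPB data, on taking the recommendation of 50 as the protocol reports it, and, for the precision figures, on a pooled SD from two arms with roughly normal data.

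**What to change.** Reword the Sample size section to say that 50 participants will be randomised, and that about 43–44 are expected to have SPPB measured at 8 months at the Green retention limit and about 36 in the Amber case. State that the SD will be given with a 95% confidence interval for the number actually measured, and report that interval wherever the SD is carried into the definitive sample size calculation.

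The cost is wording only. No extra patients, visits or assessments are needed, and the change can be made with recruitment under way. The only price is a slightly less favourable stated number of measured participants. Recruiting enough to have 50 measured would instead take 59 at 15% loss, but the size of the effect does not call for that.
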